### Ethical Considerations

The protocol (2019-11-22) has been approved by the Comité de Protection des Personnes Nord-Ouest I–Université de Rouen (2019-A00395-52), which is part of the French national ethical committee. Written informed consent will be collected from each older adult before their participation. The study is registered on ClinicalTrials.gov under the number NCT04134988 (2019/10/22) and in the Commission Nationale de l'Informatique et des Libertés, which verifies the legality and security of computerized personal data in France.

### Rehabilitation Programs

Both rehabilitation programs (intervention and control) will be consistent with the prescription of the participants’ physicians. For each group, the program will be guided by a psychomotor therapist and will last 8 weeks, with 35-minute individual sessions twice per week. According to professional practices in psychomotor therapy, the psychomotor therapist will ensure the progress of each group’s sessions by adapting their proposals to the participant.

#### Intervention Group: Medimoov Sessions

The Medimoov gaming platform [15] is a physio-gaming medical device that works using functional and postural rehabilitation software. The therapy requires a computer equipped with Medimoov, a Kinect camera, a projection screen, and an immersive sound system (Figure 1). Each participant has their own profile in which their age, gender, and physical capacities (eg, their amplitude of movement) are stored (Figure 2). Each game’s required movements are adjusted to the participant’s capacities with personalized calibration. Medimoov offers 14 exercises (eg, upper limb work, sit-to-stand exercises) within 6 different games that can be configured according to specific conditions (eg, spatial neglect) and different cognitive statuses (eg, simplified decor to avoid distraction for people with limited attention capacities). The length of each game can also be configured according to the participant’s stamina.

**Figure 1 figure1:**
[figure not shown]
(A) The large screen displays an exergame. The Kinect camera is positioned above the screen to capture the movements of the participant; the computer with the Medimoov platform is on the left of the screen. (B) The harness protects the participants from injury if they fall during the session.

The program will last 8 weeks, with biweekly individual sessions of 35 minutes for a total of 16 sessions. The personal calibration and the creation of the participant’s profile will be performed during the first session. The psychomotor therapist will systematically offer the use of a harness before the beginning of the session. This harness, which is hung from a rail system, secures the person while they are standing and during motor activity. The psychomotor therapist will adapt their proposals to the participant according to his/her professional practice. The sessions will be conducted in the following order: (1) sessions 1 to 4, work on the cervical spine and upper limbs while seated; (2) sessions 5 to 8, in a sitting position, work on limb movement amplitude and precision and movement of the spine as a whole; (3) sessions 9 to 12, work on the spine as a whole with a special focus on the cervical spine with static and dynamic balance in the standing position; and (4) sessions 13 to 16, work on the movement amplitude and precision with static and dynamic balance in the standing position.

**Figure 2 figure2:**
[figure not shown]
(A) Medimoov allows calibration of its games according to the participant’s abilities. The instructions for the movements to be performed are displayed on the screen. The orange circle indicates the participant’s maximum range of motion, and a feedback image reconstructing the movements captured by the Kinect is presented at the bottom of the screen. (B) Several games can be played. For one of the games, the participant leads a pirate ship to recover gold coins while avoiding rocks and enemy fire. (C) Each participant has a personal profile in which the psychomotor therapist can access the participant’s session and performance history.

#### Control Group: Traditional Psychomotor Therapy Sessions

Parallel to the intervention group, the program will last 8 weeks, with biweekly sessions of 35 minutes for a total of 16 sessions. This traditional psychomotor therapy rehabilitation program will be the one that is usually conducted in the ward. As in the intervention group, the psychomotor therapist will ensure the progress of the sessions by adapting their proposals to the participant according to their professional practice. The individual sessions will be based on the following progression. (1) Sessions 1 to 4, body waking exercises, soft gymnastics with cervical spine and upper limb mobilizations in a seated position; (2) sessions 5 to 8, upper and lower limb movement coordination exercises in a seated position and movement of the spine as a whole; (3) sessions 9 to 12, static and dynamic balance exercises with work on the spine as a whole with a special focus on the cervical spine in a standing position; (4) sessions 13 to 16, in the standing position, psychomotor trails (movement amplitude and precision).

### Study Outcome and Measures

Sociodemographic data will be collected from the participants’ medical records and will include the following: age, gender, highest education level, living conditions (eg, alone or with relatives, at home or in long-term care), reason for hospitalization, the presence of visual or hearing impairment, and the number of falls during the past 12 months. Clinical evaluations will focus on the following: (1) balance and risk of falls (Score Physical Performance Battery [SPPB] test, One-Leg Stand test, Timed Up and Go [TUAG]), (2) fear of falling (Short FES-I) and (3) cognitive evaluations (Stroop test, Trail Making Test Parts A and B). Wrist actimetry will be used to assess all older adults’ spontaneous motor activity outside rehabilitation sessions (eg, engaging in their activities of daily living, walking indoors in their room and the common areas of the ward, or walking outdoors in the hospital garden). The study procedure and assessment schedule are presented in Table 1.

**Table 1 table1:** The study procedure is presented following the SPIRIT (Standard Protocol Items: Recommendations for Interventional Trials) template.

Phase and time point (week)			Enrollment		Allocation		Postallocation					End	
				Week 0		Week 1			Week 4		Week 8		
**Enrollment**													
	Eligibility screening	✓											
	Informed consent	✓											
	Allocation			✓									
**Interventions**													
	Medimoov or standard psychomotor therapy												
**Assessments**													
	Timed Up and Go					✓			✓		✓		
	One-Leg Stand					✓			✓		✓		
	Short Fall Efficacy Scale					✓			✓		✓		
	Stroop					✓			✓		✓		
	Trail Making Test Parts A and B					✓			✓		✓		
	Score Physical Performance Battery					✓			✓		✓		
	Actimetry					✓			✓		✓		
	Satisfaction questionnaire^a^										✓		

^a^This assessment is specific to the intervention group.

### Assessments

#### The FES-I

This 5-minute questionnaire [34] is composed of 7 questions on daily activities and focuses on fear of falling. Each question can be scored between 1 (“Not at all concerned”) to 4 points (“Very concerned”). Compared to the Activities-Specific Balance Confidence Scale and the Geriatric Fear of Falling Measurement, the FES-I had the best internal consistency [35]. The 4-week test-retest fidelity, measured by an intraclass correlation coefficient (*r*), is 0.83 [30]. Although the FES-I lacks responsiveness among nonfrail older adults, it has been chosen here because hospital inpatients are often frail [35]. As this scale is often used in other experimental studies, using it will allow the results of this study to be compared with those of previous studies [36-39].

#### The TUAG test

This test [40] consists of standing up from a chair with armrests, walking 3 meters, turning around, and coming back to sit. The test lasts less than 5 minutes. A shorter time of execution of the test indicates a better balance and stability and a lower risk of falls; the time of execution is thus analyzed as a quantitative value indicating the risk of falls. Risk of falls is identified if the duration of the test is longer than 20 seconds. The 2-week test-retest fidelity, measured by an intraclass correlation coefficient (*r*), ranges between 0.93 and 0.99 [40]. Compared to other assessment tools for risk of falls, such as the One-Leg Stand test, the Functional Reach test, and the Tinetti test, the TUAG has demonstrated better discriminant validity for fall prediction [40]. When compared to the Berg Balance Scale and the Tinetti test, the TUAG test has demonstrated the best sensitivity to change (93%) [41]. It has also demonstrated a higher participation rate than the One-Leg Stand test and the Functional Reach test [40]. For these reasons, it has been chosen as the primary outcome for this study.

#### The SPPB Test

This 5-minute test [42] focuses on static balance, walking, lower-limb strength and risk of falls. This functional assessment has a predictive value for the evolution of the patient's health and autonomy in daily activities after hospital discharge [43]. It provides information on the patient’s balance, quality of walking, and risk of falling. The score varies between 0 and 12; a score <6 indicates low performance and a high risk of falling. The 5-day test-retest fidelity is *r*=0.89 [44]. The test has been chosen for its good responsiveness to change [45].

#### The One-Leg Stand Test

This test [40] consists of standing on one leg for as long as possible on each side. A longer time on one leg indicates a better balance ability. As with the TUAG, the time can be analyzed as a quantitative indicator of risk of falling and quality of walking. For healthy older adults aged between 70 and 79 years, the mean duration is 15.0 seconds (SD 13.9); for healthy older adults aged between 80 and 99 years, the mean duration is 6.2 seconds (SD 9.3). The 2-week test-retest fidelity, measured by an intraclass correlation coefficient (*r*), ranges between 0.93 and 0.99 [40]. Measured by effect size, the One-Leg Stand test has demonstrated a lower sensitivity to change than the TUAG test; thus, it will not be a primary endpoint for this study [40].

#### Actimetry

The participants’ motor activity will be measured continuously for 3 consecutive days by actimetry using a watch that contains accelerometers (Vivago Ltd) worn on the nondominant wrist. Acceleration of movements will be recorded and stored in the watch as arbitrary units per second. For analysis purposes, activity units will be grouped in 3-hour periods during the day (midnight to 2:59 AM, 3 to 5:59 AM, 6 to 8:59 AM, 9 to 11:59 AM, noon to 2:59 PM, 3 to 5:59 PM, 6 to 8:59 PM, and 9 to 11:59 PM). For each participant, the average activity during the 3 days will be calculated based on these 3-hour periods. This innovative exploratory method will not be considered as an endpoint of the study. The aim is to explore how rehabilitation can influence spontaneous mobility in each group and to explore whether it is associated with a decrease in the fear of falling.

#### The Stroop Test

This test [46] is a 5-minute test to evaluate response inhibition capacities. It will be scored by calculating interference indicators and the *z* score, which adjusts the time required to complete the test to the expected performance, taking into account the age and education level of the participant [47]. The *z* score indicates a deficit in response inhibition (score inferior to –1.65), a limitation in response inhibition (score between –1.64 and –0.9), medium inhibition capacities (score between –0.9 and 0.9), superior response inhibition capacities (between 0.9 and 1.64), and highly superior response inhibition capacity (>1.65) [47]. The test-retest fidelity, measured by the intraclass correlation coefficient (*r*), ranges between 0.84 and 0.91 [48], and the meta-analyses of Demakis et al (2004) [49] demonstrated that the Stroop test is sensitive to change.

#### The Trail Making Test Parts A and B

This evaluation [50] focuses on executive functions, including number and letter recognition, cognitive flexibility, visual scan, and motor functions. This evaluation lasts 10 minutes. The score represents the amount of time required to complete parts A and B of the test [50]. Scores are then compared to standards that take into account age and educational level [50]. The test-retest fidelity, measured by the intraclass correlation coefficient (*r*), ranges between 0.76 and 0.94 [51]. In their literature review, Pointrenaud et al (1997) [52] demonstrated that the Trail Making Test is sensitive to change.

#### Documentation of Falls

Adverse events and falls during hospitalization will be documented with their date and severity.

#### Satisfaction Questionnaire

Within the intervention group, participants will answer a satisfaction questionnaire focusing on Medimoov and the exergaming aspect of their rehabilitation. Their answers will be useful to better interpret the results of this pilot study. The satisfaction questionnaire is composed of 10 5-level Likert-type questions; its aim is to evaluate the participants’ experience and their self-confidence after the exergame-based rehabilitation program. The questionnaire takes approximately 2 minutes to complete.

### Study Procedures

Three assessments will be performed by a psychomotor therapist (who is not one of the therapists involved in the rehabilitation program) focusing on physical and cognitive capacities. The first assessment will be performed during the first week, before the start of the rehabilitation program; the second will occur during week 4; and the third will occur during week 8, at the end of the rehabilitation program. Assessments will be blinded; the assessors will not know the assigned group of each participant. To preserve neutrality, assessments will be performed in a different room than the sessions.

#### Endpoints

The primary clinical endpoint is the comparison of the changes in FES-I scores between the two groups. The main secondary endpoint is the comparison of changes in TUAG scores between the groups. Other secondary endpoints are a significantly greater improvement in the One-Leg Stand test, the SPPB test, the Trail Making Test Parts A and B, and the Stroop test in the intervention group and a high level of satisfaction in the intervention group.

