Medimoov (NaturalPad) [24] is a movement-based video game for rehabilitation of older adults that allows the therapist to choose the movements the patient will perform to interact with the game. The difficulty and the speed of the game can be defined by the therapist, allowing for a fine-tuned personalization of the sessions according to the patient’s progress. A preliminary study showed that using Medimoov’s personalized activities may positively influence older adults’ functional ability and motivation [15]. Most existing studies evaluating the use of exergames do not involve an appropriate control group (ie, a control group following the standard rehabilitation program) [17,21] or do not involve an exergame specifically designed for rehabilitation of older adults that allows for the personalization of the sessions [21,22,25]. Thus, this study aims to evaluate the effects of Medimoov on older adults with fear of falling compared with standard psychomotor rehabilitation as prescribed by physicians. Two aspects of the rehabilitation will be explored: the preventive function (decreased risk of falls) and the therapeutic function (decrease of fear of falling and increase of motivation during rehabilitation).

The main objective is to evaluate the efficacy of exergames played on the Medimoov platform on fear of falling and risk of falls. The secondary objective is to assess the effect of the exergame intervention on the participants’ executive functions during the study. Another secondary objective is to explore the perception of exergame-assisted rehabilitation by the participants of the intervention group. The hypothesis is that exergames in rehabilitation can lead to decreased fear of falling and risk of falls due to an improvement of balance, physical functions, and executive functions, including an improvement in cognitive inhibition.

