### Participants and Recruitment

The research project will be conducted in two intermediate-care wards for older adults at the Charles Foix Hospital, a French geriatric hospital. Guidelines to calculate the sample size do not exist in the literature yet; thus, the sample size has been estimated based on previous studies evaluating fear of falling–focused interventions [28,29]. A sample size of 20 participants per group is often reported. A total of 25 participants per group will be recruited to factor in a potential 20% withdrawal or other variations. Recruitment will be conducted among hospitalized patients in intermediate-care rehabilitation hospital wards. The inclusion criteria will be as follows: (1) age of 65 years or older, (2) ability to understand and answer short and simple questions (as determined by the clinical interview), (3) ability to stand upright in a bipedal position, feet together, for longer than 1 minute with or without a technical aid, (4) a score of 13 or greater on the FES-I [30] (moderate or severe fear of falling), (5) stable medical condition, and (6) ability to give written consent. The exclusion criteria will be as follows: (1) cannot correctly distinguish the elements on the screen, (2) in palliative care, (3) under a legal protection measure, (4) obtained a score <16 on the Mini Mental State Examination (MMSE) [31], and (5) recently underwent orthopedic surgery (<2 months); the latter is an exclusion criterion because it requires specific rehabilitation programs [32]. The MMSE will be used for screening purposes only to exclude patients with severe cognitive disorders that would prevent them from participating. Participation may be interrupted at the participant’s request or if the participant experiences an adverse health event (eg, stroke). All patients hospitalized in the rehabilitation ward at the beginning of the study will be screened for eligibility by their physicians, and if eligible, will be asked to participate after a detailed presentation of the protocol by a postdoctoral fellow or a research professional. The eligibility of the patients admitted to hospital after the start of the study will be verified. Participant recruitment will be ongoing until the sample number (N=50) is reached. Eligible patients will receive a letter of information. A random selection will be conducted if the number of eligible patients is higher than the number of required participants.

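### The TUAG section and the Endpoints section name different primary outcomes, and nothing in the protocol says which governs

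*Protocol article*

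**What the plan says.** Three places in the Methods bear on which outcome is primary.

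- **Endpoints:** "The primary clinical endpoint is the comparison of the changes in FES-I scores between the two groups". The next sentence reads: "The main secondary endpoint is the comparison of changes in TUAG scores between the groups".
- **Assessments, The TUAG test:** after citing discriminant validity, sensitivity to change and participation rate in favour of TUAG, the section concludes: "For these reasons, it has been chosen as the primary outcome for this study".
- **Assessments, The One-Leg Stand Test:** this test "has demonstrated a lower sensitivity to change than the TUAG test; thus, it will not be a primary endpoint for this study".

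The Introduction does not rank the two constructs: "The main objective is to evaluate the efficacy of exergames played on the Medimoov platform on fear of falling and risk of falls". The FES-I section gives reasons for using that scale but never calls it primary. Strengths and Limitations mentions primary and secondary outcomes without naming them. Statistical Analysis applies the same tests to all endpoints and gives no order.

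The Endpoints section words the remaining physical and cognitive endpoints as a hoped-for result, a significantly larger gain in the intervention arm, and lists a high level of satisfaction beside them.

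**The concern.** A trial with one primary outcome is judged on that outcome. Here the only argued case for a primary supports TUAG, while the section that formally lists the endpoints names FES-I. A reader of the eventual report could not tell from this document which result was meant to decide the trial.

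The choice matters because the two measures differ in kind. FES-I is a questionnaire answered by participants who know their allocation (the Design section calls the trial open), and Strengths and Limitations concedes that desirability bias can occur. TUAG is a timed performance test given by an assessor who is blinded according to Study Procedures. The two could plausibly disagree. If they did, either could be presented as the primary result with support from the text, and the primary comparison would have no single controlled error rate.

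**Working it through.** **1. The statements side by side**

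| Section | Status of FES-I | Status of TUAG |
|---|---|---|
| Endpoints | primary | main secondary |
| The TUAG test | not mentioned | primary |
| The One-Leg Stand Test | not mentioned | benchmark for ruling out another test as primary |
| The FES-I | used, no rank given | not mentioned |
| Introduction, main objective | fear of falling, unranked | risk of falls, unranked |

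The first two rows conflict. A co-primary reading fails because the Endpoints section expressly makes TUAG secondary.

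**2. Does the sample size settle it?** Participants and Recruitment says: "A sample size of 20 participants per group is often reported" and "A total of 25 participants per group will be recruited to factor in a potential 20% withdrawal or other variations". The arithmetic reproduces: 20 / (1 − 0.20) = 25 per group, 50 in total. The 20 comes from earlier studies of fear-of-falling interventions, with no effect size, standard deviation, significance level or power for either outcome. The source of the precedent leans to FES-I, but the number itself does not depend on which outcome is primary.

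**3. Other pointers.** Entry requires a score of 13 or more on the fear-of-falling scale, which also leans to FES-I. No comparable TUAG threshold is used for entry.

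**4. Error rate if either outcome could count as primary.** The inputs are assumptions, because the article gives no significance level, sidedness or correlation: each test two-sided at 5% (critical value 1.96), no true effect on either outcome, and test statistics bivariate normal with correlation ρ.

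P(at least one significant) = 1 − P(|Z₁| < 1.96 and |Z₂| < 1.96)

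At ρ = 0 this is 1 − 0.95² = 0.0975. For ρ > 0 the joint probability comes from the bivariate normal distribution:

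| ρ | Chance of a false-positive primary |
|---|---|
| 0 | 9.75% |
| 0.3 | 9.5% |
| 0.5 | 9.1% |
| 0.7 | 8.4% |
| 0.9 | 7.0% |

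With a single primary fixed in advance the figure is 5%. Counting only results that favour the intervention, the figures are 4.9% at ρ = 0 and 3.5% at ρ = 0.9, against 2.5%.

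**The case against.** The strongest reply is that the Endpoints section exists to rank outcomes and does so plainly, while the TUAG sentence sits in an instrument description and may be a leftover. The entry threshold and the sample-size precedent support that reading. This makes FES-I the likelier intention. But no text gives the Endpoints section precedence, and the One-Leg Stand section shows that the TUAG statement is not an isolated slip.

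The second reply is that the article describes a pilot and an exploratory study, and defers a proper power calculation to a larger trial. That reduces the weight of any error-rate argument. It does not excuse two incompatible primaries in a study that names a primary endpoint, sets out to evaluate efficacy and is meant to be the basis for larger trials. A fuller protocol or a SAP might fill a silence, but it would not make these two statements agree.

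Four stronger readings are tempting and are not supported:

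- **That the visit is open, so week 4 or week 8 could be picked.** The endpoint sentence names no visit. But Statistical Analysis compares pre- with postintervention data and ties imputation to withdrawal before the eighth week, and Study Procedures places the third assessment in week 8, at the end of the program. Week 8 is implied and needs only confirming.
- **That the main objective is itself contradictory.** An objective naming two constructs is compatible with one primary and one main secondary endpoint.
- **That the plan provides for choosing the primary after seeing results.** It does not. The text leaves that possibility open, and nothing suggests intent.
- **That the error rate is 9.8%.** That is the zero-correlation end of a range and rests on an assumed significance level.

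**Conclusion.** The contradiction is real, stands in the current text and needs no calculation to establish. TUAG is declared primary in one section and main secondary in another, and FES-I is declared primary in the second. The document as a whole leans to FES-I without settling the matter.

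The possible inflation runs from 7.0% (correlation 0.9) to about 9.8% (correlation 0), against 5%. It is conditional on a two-sided 5% level for each test and on either outcome being allowed to count. The exploratory pilot status tempers this consequence. The correction is still necessary, because without it the document does not determine which result decides the trial.

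**What to change.** Before any data are analysed:

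1. In Endpoints, state one primary endpoint: the between-group comparison of change in Short FES-I (the 7-question form) from baseline to week 8. This keeps change from baseline, as the section already has it, and makes the implied visit explicit.
2. In The TUAG test, delete or correct the sentence that calls it the primary outcome. Keep TUAG change from baseline to week 8 as the main secondary endpoint.
3. In The One-Leg Stand Test, align the reasoning so that it no longer implies TUAG is primary.
4. State the other endpoints measured in both arms as between-group differences rather than as a hoped-for significant result. Satisfaction is collected only in the intervention group, so report it descriptively there.

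If the sponsor really wants both outcomes to decide the trial, that must be declared and the significance level split. At 2.5% each, the chance of any false positive is 1 − 0.975² = 4.9% if the tests are uncorrelated. The price is sensitivity: with 20 per group and 80% power, the detectable standardized difference, (z for the significance level + z for power) × √(2/20), rises from (1.960 + 0.842) × 0.316 = 0.89 to (2.241 + 0.842) × 0.316 = 0.98. Keeping a single primary avoids this.

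The cost of the main fix is wording only. The Results section reports 10 of 50 participants enrolled as of October 2020 and no analyses started, so on the article's own account the change can be made without knowledge of results. The registry entry was not available, so whether it also needs correction is unknown.
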